#### 2.11.3 Cost-utility analysis

The economic evaluation will be reported according to the Consolidated Health Economic Evaluation Reporting Standards statement (Husereau et al., 2013) and the Good Research Practices for Cost-Effectiveness Analysis Alongside Clinical Trials (Ramsey et al., 2015). The approach we will follow is estimating costs from the healthcare and the government perspectives, taking the previous 6 months as the time frame. Catalonia has full governance of health and social care and, as in every other Spanish region, healthcare is universal and publicly financed. The government perspective includes both direct healthcare costs assumed by the Catalan government (excluding out-of-pocket costs and costs associated with private insurance) and indirect costs related to productivity losses assumed by the Spanish government. The healthcare perspective includes only direct healthcare costs. Costs will be estimated for the 6 months before starting the intervention (at baseline assessment) and for the 6 months before the follow-up assessment.

Direct costs will be calculated as the sum of medication costs and health service use (primary, specialized and emergency care consultations, hospital admissions) and cost of staff to run the interventions. The cost of medication will be calculated by determining the price per milligram during the study according to the Vademecum International (Red Book), and including VAT. Total medication costs will be computed by multiplying the price per milligram by the daily dose in milligrams and the number of days receiving the specified treatment. The unit costs of medical tests and health services will be obtained from the SOIKOS health database (http://www.oblikue.com/bddcostes/). Indirect costs (lost productivity) will be computed according to the human capital approach, by multiplying the minimum daily wage in Spain in 2022 by the number of days on sick leave reported by each participant. Unit costs will be reported in Euros (€).

The utilities represent the rating of the patients’ quality of life on a scale from 0 (“as bad as death”) to 1 (“perfect health”). For the cost-utility analysis, the ratio between the cost of each intervention and its consequences in terms of QALYs will be calculated. QALYs will be computed using Spanish EQ-5D tariffs. Following the International Society for Pharmacoeconomics and Outcomes Research (ISPOR) core recommendations for cost-effectiveness analyses alongside RCTs (Ramsey et al., 2015), we will calculate the incremental cost-utility ratios (ICUR) for each pairwise comparison (TAU vs. FIBRO-On, TAU vs. FIBRO-Out, FIBRO-On vs. FIBRO-Out), defined as the difference in mean costs divided by the difference in mean QALYs. Given that the duration of the study is 6 months, neither costs nor outcomes are subject to discounting. QALYs at 6 months after the start of the interventions will be approximated by calculating the area under the curve.

Cost-effectiveness analyses will be performed using the Zellner’s seemingly unrelated regression (SUR) model (Greene, 2003) with the STATA’s *sureg* command. Using the SUR method for cost-effectiveness purposes implies the use of a bivariate system of regressions that includes both costs and outcomes (with the latter being either QALYs or EurQol-5D-5L VAS, depending on the model considered) as the dependent variables of the two separate equations, which will be estimated jointly. The regressions of costs and outcomes are therefore part of two regressions on treatment allocation (i.e., whether they are assigned to TAU, FIBRO-Out, or FIBRO-On) plus an additional set of control variables (measured at baseline) if necessary: age, gender, marital status, education level, employment status, baseline costs, or baseline outcome, depending on the equation considered.

Estimates of incremental cost and of incremental effect values using the SUR method described above will be derived with 1,000 bootstrap replications in order to address a possible skewness in the distribution of the dependent variables (Briggs et al., 1997). We also will construct acceptability curves to represent the probability of the intervention being cost-effective, given a varying threshold for the willingness to pay for each QALY gained in each intervention compared to the others. The robustness of the cost-utility results will also be tested in different case scenarios; more precisely, we will use ITT approach as the primary analysis, imputing missing values for those variables missing at 6-month follow-up by using multiple imputation methods with the chained equations approach (Royston and White, 2015). Additional scenarios (sensitivity analysis) will be also conducted repeating the same statistical analyses in a complete case analysis, including only those participants with complete assessments at baseline and at 6-month follow-up, and in a per-protocol analysis including only those participants who attended at least 75% of the sessions (9 out of 12). STATA 16.0 statistical software will be used for cost-utility analyses.

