## Abstract

**Introduction:** The On&Out study is aimed at assessing the effectiveness, cost-utility and physiological underpinnings of the FIBROWALK multicomponent intervention conducted in two different settings: online (FIBRO-On) or outdoors (FIBRO-Out). Both interventions have proved to be efficacious in the short-term but there is no study assessing their comparative effectiveness nor their long-term effects. For the first time, this study will also evaluate the cost-utility (6-month time-horizon) and the effects on immune-inflammatory biomarkers and Brain-Derived Neurotrophic Factor (BDNF) levels of both interventions. The objectives of this 6-month, randomized, controlled trial (RCT) are 1) to examine the effectiveness and cost-utility of adding FIBRO-On or FIBRO-Out to Treatment-As-Usual (TAU) for individuals with fibromyalgia (FM); 2) to identify pre–post differences in blood biomarker levels in the three study arms and 3) to analyze the role of process variables as mediators of 6-month follow-up clinical outcomes.

**Methods and analysis:** Participants will be 225 individuals with FM recruited at Vall d’Hebron University Hospital (Barcelona, Spain), randomly allocated to one of the three study arms: TAU vs. TAU + FIBRO-On vs. TAU + FIBRO-Out. A comprehensive assessment to collect functional impairment, pain, fatigue, depressive and anxiety symptoms, perceived stress, central sensitization, physical function, sleep quality, perceived cognitive dysfunction, kinesiophobia, pain catastrophizing, psychological inflexibility in pain and pain knowledge will be conducted pre-intervention, at 6 weeks, post-intervention (12 weeks), and at 6-month follow-up. Changes in immune-inflammatory biomarkers [i.e., IL-6, CXCL8, IL-17A, IL-4, IL-10, and high-sensitivity C-reactive protein (hs-CRP)] and Brain-Derived Neurotrophic Factor will be evaluated in 40 participants in each treatment arm (total n = 120) at pre- and post-treatment. Quality of life and direct and indirect costs will be evaluated at baseline and at 6-month follow-up. Linear mixed-effects regression models using restricted maximum likelihood, mediational models and a full economic evaluation applying bootstrapping techniques, acceptability curves and sensitivity analyses will be computed.

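### The three-arm cost-utility plan specifies only pairwise ratios, with no dominance step, and leaves unclear whether its acceptability curves are pairwise or three-way

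*Protocol article*

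**What the plan says.** All references are to the protocol article.

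- **Design (Abstract).** Participants are "randomly allocated to one of the three study arms: TAU vs. TAU + FIBRO-On vs. TAU + FIBRO-Out".
- **Economic aim (Abstract).** The first objective is "to examine the effectiveness and cost-utility of adding FIBRO-On or FIBRO-Out to Treatment-As-Usual (TAU") for people with fibromyalgia.
- **Ratios (2.11.3).** "we will calculate the incremental cost-utility ratios (ICUR) for each pairwise comparison", and the pairs are listed as "TAU vs. FIBRO-On, TAU vs. FIBRO-Out, FIBRO-On vs. FIBRO-Out), defined as the difference in mean costs divided by the difference in mean QALYs".
- **Model (2.11.3).** Costs and outcomes are estimated jointly by seemingly unrelated regression (SUR), as "two regressions on treatment allocation (i.e., whether they are assigned to TAU, FIBRO-Out, or FIBRO-On"). Allocation therefore enters with three levels.
- **Uncertainty (2.11.3).** Incremental costs and effects "will be derived with 1,000 bootstrap replications". The investigators will also "construct acceptability curves to represent the probability of the intervention being cost-effective". The only description of which options these curves compare is the phrase "given a varying threshold for the willingness to pay for each QALY gained in each intervention compared to the others".

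Section 2.11.3 has no ordering of the arms by cost, no dominance or extended-dominance rule, and no comparison of net benefit across all three arms. It does not say whether the curves are drawn pair by pair or for three options at once. It names no single willingness-to-pay value.

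**The concern.** For any one patient the three arms are alternatives, as they are in the randomisation, and Table 1 describes the two programmes as equivalent in content. Section 1.1 names the lack of a parallel comparison between formats as a gap to fill. The Discussion (section 3) foresees public funding of one or both programmes if the results are good. A payer will therefore ask which of the three to offer, as well as whether each programme beats TAU.

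Two things can go wrong if the results stay pairwise:

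1. **Ratios.** A programme can have an acceptable ratio against TAU and still be the best choice at no threshold, because the other programme yields more QALYs at a better rate (extended dominance). The ratio between the two programmes can then look more favourable than the ratio that matters.
2. **Curves.** A pairwise curve gives the probability of beating one comparator. The probability of being the best of three is a joint probability, which pairwise curves do not determine.

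**Working it through.** The plan gives no cost, QALY or standard error, so there is no figure of its own to reproduce. Every cost, QALY and probability input below is assumed for illustration. Only the three arms, the three pairs, the three-level SUR and the 1,000 replicates come from the protocol article.

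Throughout, with λ as willingness to pay per QALY: NMB = λ × QALY − cost.

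**Step 1. Do the three pairwise contrasts identify the best arm by point estimate?** Yes. Pairwise differences in NMB are additive, NMB(Out) − NMB(TAU) = [NMB(Out) − NMB(On)] + [NMB(On) − NMB(TAU)], so the ordering is transitive. In 100,000 random three-arm cost and QALY sets, at λ = 10,000, 20,000, 30,000 and 50,000, one arm always won both of its contrasts, and it was the highest-NMB arm in 100% of sets.

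**Step 2. Can the ratios alone mislead?** Assume:

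| Arm | Cost (€) | QALYs |
|---|---|---|
| TAU | 1,500 | 0.300 |
| FIBRO-On | 1,800 | 0.310 |
| FIBRO-Out | 2,000 | 0.330 |

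- On vs TAU: 300 / 0.010 = 30,000 €/QALY
- Out vs TAU: 500 / 0.030 = 16,667 €/QALY
- Out vs On: 200 / 0.020 = 10,000 €/QALY

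NMB by arm:

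| λ | TAU | On | Out | Best |
|---|---|---|---|---|
| 15,000 | 3,000 | 2,850 | 2,950 | TAU |
| 20,000 | 4,500 | 4,400 | 4,600 | Out |
| 30,000 | 7,500 | 7,500 | 7,900 | Out |

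From λ = 30,000 upwards, On looks acceptable against TAU, yet it is the best option at no λ: TAU is best below 16,667 and Out above it. On is extendedly dominated. The relevant ratio for Out is 16,667, and the 10,000 against On understates it.

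**Step 3. How far is a pairwise probability from a three-way one?** Let the NMB estimates of the three arms be independent and normal with equal variance s². Each difference from TAU then has variance 2s², and the two differences share covariance s² through TAU, so their correlation is s²/2s² = 0.5.

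- Standardised gain 0.84 for both programmes: pairwise probability against TAU is Φ(0.84) = 0.80. TAU is best only if both differences are negative, with probability 0.087. Each programme is best with probability (1 − 0.087)/2 = 0.456.
- Standardised gain 0.50 for both: pairwise Φ(0.50) = 0.69, TAU best 0.163, each programme (1 − 0.163)/2 = 0.418.
- Unequal programmes, with gains of 1 and 1.5 in units of one arm's standard error (1,000,000 draws): On vs TAU 0.76, Out vs TAU 0.86, Out vs On 0.64. Best of three: TAU 0.08, On 0.33, Out 0.59.

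**Step 4. Would all three pairwise curves together give the answer?** They narrow it without fixing it. In the 0.80 case the On-vs-Out curve reads 0.50 by symmetry. The probability that On is best can be no more than the smaller of 0.80 and 0.50, which is 0.50, and no less than 0.80 + 0.50 − 1 = 0.30. Where it falls between 0.30 and 0.50 depends on the joint distribution, which the bootstrap replicates carry and the pairwise curves discard.

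**The case against.** A reader might infer that the plan cannot show which arm is the best buy and that its curves are certainly pairwise. The documents support neither.

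- All three pairs are planned, FIBRO-On against FIBRO-Out included, and Step 1 shows that their incremental costs and QALYs identify the best arm by point estimate. This stands.
- The wording on the curves sets each intervention against the others, which can mean three-way curves. Only the ratios are stated to be pairwise. This stands, and it makes the curves ambiguous rather than wrong.
- The three-level SUR with bootstrapping is already planned, so the replicates for a three-way result will exist. This stands. What is left is tabulation and plotting.
- In the equal-programmes illustration, the planned On-vs-Out curve would itself sit at 0.50 and warn that neither programme is preferred. This stands in part. The warning is real, but the probability of being best of three remains undetermined (Step 4).
- The objective is the cost-utility of adding either programme to TAU, and the Discussion allows that one or both may be adopted. Contrasts with TAU answer that question and should stay. It does not remove the choice between two formats of the same content.
- This is a condensed article that commits to published reporting standards for economic evaluations, and a fuller analysis plan may settle the layout. That is fair for the curve format. The ratios, however, are specified in the article as pairwise, alongside the model, the software command and the number of replicates.

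**Conclusion.** The point holds at modest weight. As written, the plan fixes pairwise ratios for a three-option decision without a dominance step, and its acceptability curves can be read two ways. Ratios alone could present an extendedly dominated programme as acceptable, as in the assumed example where On has 30,000 €/QALY against TAU but is optimal at no threshold. If the curves are pairwise, they would not report the probability of being best of three. That gap is about 0.80 against 0.46 for two equally good programmes, assuming normal net benefit and a correlation of 0.5 through the shared TAU arm.

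The sizes are illustrative, since the plan gives no economic inputs. The trial data, the SUR model, the sample size and the clinical analyses are not affected. The gain is a clearer basis for the adoption conclusion that the Discussion foresees.

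**What to change.** In section 2.11.3, or in the economic analysis plan:

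1. Keep the three pairwise ratios as supporting output, always with their incremental costs and incremental QALYs.
2. Add one incremental table. Order the arms by mean cost, remove dominated and then extendedly dominated arms, and give each remaining arm's ratio against the next less costly remaining arm.
3. State that the acceptability curves are three-way. In each of the 1,000 bootstrap replicates of the three-level SUR, compute net monetary benefit for all three arms over the range of thresholds. Equivalently, set TAU to 0 and use each programme's incremental net benefit. Plot the share of replicates in which each arm is highest, so that the curves sum to 1 at every threshold.
4. Do this for both planned perspectives, healthcare and government.

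The cost is a few lines of code on replicates that are already planned. No new data, participants or models are needed.

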#### 2.11.4 Analysis of changes in biomarkers

The effect of interventions on immune-inflammatory markers and BDNF levels will be evaluated also with REML. In those cases where cytokine concentrations are under detection level of the test, the detection limit value will be assigned. Cytokines, hs-CRP and BDNF values will be subjected to a natural logarithmic transformation to normalize the significantly skewed data distributions. In order to comprehensively integrate pro-inflammatory with anti-inflammatory markers, indexes indicative of inflammatory balance will be calculated (e.g., IL-6/IL-10, CXCL8/IL-10 and hs-CRP/IL-10) in a similar way to previous studies (Andrés-Rodríguez et al., 2019). Since some pharmacological treatments such as antidepressants are reported to potentially affect some cytokine levels (Hannestad et al., 2011), differences in such levels between patients taking vs. not taking these drugs will be also evaluated. In case of any statistically significant effect, antidepressant status (“taking” = 1, “not taking” = 0) will also be included as a co-variable in the REML analyses for each specific biomarker.

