### 2.3 Sample size calculation

Two-hundred and twenty-five individuals who meet the selection criteria for the study will be recruited. The estimated sample size needed is n = 63 participants per condition considering a moderate effect size (Cohen’s d = 0.5) for the difference between the active arms at post-intervention compared to the control group for the primary variable (i.e., FIQR score) with an alpha = 0.05 and 1-b power = 0.80. With an expected dropout rate of 20%–25%, the final sample size is estimated at 75 individuals per arm. The effect size used for the sample size calculation corresponds to the average effect size for multicomponent interventions in FM vs. control group (Nüesch et al., 2013). Previous RCTs evaluating the FIBROWALK intervention indicated effect sizes between d = 0.4 (Serrat et al., 2021a) and d = 1.83 (Serrat et al., 2020). Using as a reference previous studies of the group evaluating the effect of different non-pharmacological treatments in FM patients on blood values of immuno-inflammatory markers (Andrés-Rodríguez et al., 2019; Montero-Marin et al., 2020), it is estimated that a sample size of 40 subjects per arm will be sufficient to be able to detect changes in the evaluated variables.

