### 2.10 Physiological markers

Blood samples will be collected in vials which will be centrifuged and the resulting serum will be stored frozen at -80°C until analysis. All samples (pre and post) will be analyzed in a single analytical batch in order to reduce inter-assay variability (approximately 15%). Serum levels of the cytokines IL-6, CXCL8, IL-4, IL-10, IL-17A and hs-CRP will be assessed. For the quantification of cytokines, Milliplex^®^ reagents from MerckMillipore analyzed on a Luminex^®^ platform will be used. The highly sensitive Human High Sensitivity T Cell multiplex kit will be used (catalogue number: HSTCMAG28SPMX11). The hs-CRP will be quantified by turbidimetry on a Siemens Atellica autoanalyzer. BDNF levels will be evaluated using an ELISA kit (reference SEA011Hu-96T). Sample analysis will be performed by the Echevarne Laboratory. Detection concentration ranges: IL-6 (0.64–10,000 pg/ml), CXCL8 (0.64–10,000 pg/ml), IL-4 (0.64–10,000 pg/ml), IL-10 (2.6–40,000 pg/ml), IL-17A (1.3–20,000 pg/ml), hs-CRP (0.1–50 mg/L), and BDNF (31.2–2,000 pg/ml). Biomarkers will be assessed only at baseline and post-intervention because of the following reasons: a) evidence of changes in immune-inflammatory markers and BDNF levels after non-pharmacological interventions with a similar duration (Sanada et al., 2015; Montero-Marín et al., 2019; Pérez-Aranda et al., 2019); b) lower risk of sample loss (vs. assessing at 6 months); c) possibility to use pre-post change as a mediator of clinical changes at 6 months follow-up; and d) budget constraints.

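### Assigning the detection limit to undetected cytokine values biases log-scale group differences toward zero, by an amount set by an unstated share of non-detects, and can bias the IL-10 ratios in either direction

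*Protocol article*

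**What the plan says.** Section 2.11.4 sets out the biomarker analysis in three steps.

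- **Non-detects:** "In those cases where cytokine concentrations are under detection level of the test, the detection limit value will be assigned".
- **Scale:** "Cytokines, hs-CRP and BDNF values will be subjected to a natural logarithmic transformation to normalize the significantly skewed data distributions".
- **Model:** "The effect of interventions on immune-inflammatory markers and BDNF levels will be evaluated also with REML". This refers back to the repeated-measures model of section 2.11.1, whose target is the group-by-time interaction. Biomarkers are measured only at baseline and post-intervention, so that interaction is the between-group difference in change.

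The same section adds that "indexes indicative of inflammatory balance will be calculated (e.g., IL-6/IL-10, CXCL8/IL-10 and hs-CRP/IL-10"). All three named indices have IL-10 as denominator.

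Section 2.10 gives the assay ranges: "IL-6 (0.64–10,000 pg/ml), CXCL8 (0.64–10,000 pg/ml), IL-4 (0.64–10,000 pg/ml), IL-10 (2.6–40,000 pg/ml), IL-17A (1.3–20,000 pg/ml"). Neither section gives an expected share of values below these limits. Section 2.3 supports the substudy size only by stating that "a sample size of 40 subjects per arm will be sufficient to be able to detect changes", with no effect size, SD, alpha or power.

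**The concern.** A value below the limit is left-censored: it is known only to lie somewhere below. Substituting the limit treats it as observed at the top of that region. A fall from just above the limit to far below it is recorded as a small fall, and a patient undetected at both visits is recorded as having no change at all. The log transformation cannot restore normality when many values sit at one point.

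Section 1.3 cites earlier reductions in IL-6 and CXCL8 after such interventions. A reduction is the direction in which limit substitution loses more of the effect. The substituted values also feed the ratio indices. They would carry over into the planned use of pre-post biomarker change as a mediator (section 2.10) and into the responder comparisons of baseline physiological variables (section 2.11.1).

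**Working it through.** **Inputs from the document.** The substitution rule, log scale, REML model and ratios (2.11.4); the limits of 0.64 pg/ml for IL-6, CXCL8 and IL-4, 2.6 for IL-10 and 1.3 for IL-17A (2.10); 40 per arm (2.3).

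**Assumptions, because the document gives no figure.** Normal log-concentrations with SD 1, pre-post correlation 0.6, shifts of about 0.5 to 0.6 SD, and a share p below the limit under no effect, varied from 2% to 60%.

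**The plan's own figures.** The 40 per arm has no inputs and cannot be reproduced. The main-trial figure can: 2 × (1.960 + 0.842)² / 0.5² = 62.8, so 63 per arm. The same formula with 40 per arm gives a detectable difference of √(2 × 7.85 / 40) = 0.63 SD at 80% power, two-sided 0.05. A true effect of 0.60 SD is therefore a reasonable test case.

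**Single marker, closed form.** For X ~ N(μ, 1) and limit L, E[max(X, L)] = LΦ(L−μ) + μ[1−Φ(L−μ)] + φ(L−μ). Randomisation makes the expected baseline difference zero, so the post-intervention difference in this mean is the expected group-by-time effect.

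Example, p = 20%: L = −0.8416.

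- Control: −0.8416 × 0.200 + 0.2800 = 0.112.
- Treated, μ = −0.60: −0.8416 × 0.4045 − 0.60 × 0.5955 + 0.3875 = −0.310.
- Difference: −0.310 − 0.112 = −0.42, and 0.42/0.60 = 70%.

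| Share below limit | Retained, true −0.60 SD |
|---|---|
| 2% | 96% |
| 5% | 91% |
| 10% | 83% |
| 20% | 70% |
| 40% | 48% |
| 60% | 29% |

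**Increase.** For +0.5 SD, the raw effect retained is 94%, 86%, 69% and 50% at 10%, 20%, 40% and 60%.

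**Standardised effect.** Substitution also shrinks the SD. Dividing by the baseline SD, a true −0.50 becomes −0.46, −0.43, −0.38 and −0.31 at 10%, 20%, 40% and 60%. A true +0.50 stays at 0.50 to 0.52.

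**Planned contrast by simulation** (40 per arm, true −0.50, 4000 runs). Limit substitution gives −0.42, −0.30 and −0.20 at 10%, 30% and 50%. Power is about 0.69 with no non-detects, then 0.63, 0.49 and 0.37. Type I error under no effect is 0.052 to 0.057.

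**Censored likelihood, same data model** (150 runs). Estimates are −0.50, −0.49 and −0.49, Monte Carlo SE about 0.02. Substituting half the limit is not a full cure: −0.50, −0.43 and −0.33.

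**Power, substituted versus censored.** In a baseline-adjusted comparison (assumed 32 per arm, true −0.60, 600 runs, Monte Carlo SE about 0.02), power is 0.75 versus 0.77, 0.67 versus 0.72, and 0.47 versus 0.53 at 20%, 40% and 60%: a gain of 2 to 6 points.

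**Ratios.** The effect on ln(IL-6/IL-10) is the IL-6 effect minus the IL-10 effect.

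- Both fall by 0.5 SD, so the true ratio effect is 0. With 10% non-detects in IL-6 and 40% in IL-10, the expected estimate is −0.423 − (−0.251) = −0.17. With the shares swapped it is +0.17; with equal shares it is 0.
- Only IL-6 falls by 0.5 SD, with 30% non-detects in each: −0.30 instead of −0.50.
- When both markers are undetected, the ratio is the constant 0.64/2.6 = 0.246 and says nothing about the patient.

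**The case against.** The strongest reply is that the size rests entirely on a share of non-detects that the document does not supply. Section 2.10 chooses a high-sensitivity kit, and section 1.2 reports raised IL-6, IL-4 and IL-17A in fibromyalgia. Neither settles the share, but both forbid assuming a high one. At 2% to 5% the loss is 4% to 9% of the effect; with no non-detects it is nil. This stands, and it makes the point conditional.

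A reader might draw four stronger conclusions that the document does not support.

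- **That the rule hides most of the effect.** This is true only from about 40% non-detects upward.
- **That it costs much power which a censored model would restore.** In the baseline-adjusted comparison the gain is only 2 to 6 points, because much of the loss comes from censoring itself. That comparison is not the planned group-by-time contrast, and the gain under that contrast may differ, so the point does not rest on power.
- **That it produces false positives for single cytokines.** Type I error stays near nominal.
- **That all biomarkers are affected.** The rule names cytokines. BDNF is untouched, and hs-CRP enters only through hs-CRP/IL-10. Section 1.3 describes IL-10 as staying higher with mindfulness training, the direction with less shrinkage.

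It can also be said that reporting non-detects and adding sensitivity analyses are details an article leaves to fuller documents. That is fair for those items, but the substitution rule itself is stated outright.

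**Conclusion.** The point holds in conditional form. If any cytokine has non-detects, the fixed rule biases its raw log-scale group difference toward zero, from slight at 5% or fewer to about half the effect at 40%. The percentages assume log-normal concentrations, a common shift and the effect sizes shown; the direction for a single marker under such a shift does not depend on the share.

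The ratios are the less predictable part. Unequal non-detect shares can create an apparent effect of either sign where none exists, so near-nominal type I error for single markers does not carry over to them. IL-10 has the highest lower limit of the five cytokines (2.6/0.64 ≈ 4 times that of IL-6 or CXCL8), but without concentrations this does not show that its share is larger.

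This is a minor-to-moderate improvement to a secondary substudy. It leaves the FIQR analysis unaffected.

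**What to change.** In section 2.11.4:

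1. For any cytokine with non-detects, analyse ln values as left-censored at the stated limit, using a censored (Tobit) mixed model with the same group-by-time fixed effects.
2. Keep limit substitution as a sensitivity analysis, and report the percentage below the limit for each marker by arm and visit.
3. Derive log-ratio effects from the censored marker models, as the difference of the two estimated effects or from a joint bivariate censored model. Taking ln(pro) − ln(anti) of substituted values carries the same bias. A difference of two censored values also has no single known limit, so a Tobit model fitted to the ratio would not solve it.
4. Treat ratios as descriptive when either marker has a substantial share of non-detects, and set that share before the data are seen.

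The cost is analysis wording and a little programming; no new data are needed. The downside is reliance on log-normality below the limit, where it cannot be checked, and possible instability for a marker that is mostly undetected.
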